### Recruitment and randomization

Block-randomization of peer groups will be done within geographical strata, each comprised of one or more counties. The size of the blocks will vary according to the number of recruited groups within each stratum. An independent researcher not involved in the study will be responsible for the randomization. Based on this randomization, peer CME groups will be assigned to either the intervention group or the control group.

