### Sample size and statistics

In a pilot study (including 13 physicians) for the present study, the mean number of positive hits on our listed QIs (Table 1) made up 25 hits per 100 elderly patients during the preceding 12 months period. In accordance with this finding, we anticipate an occurrence of inappropriate prescription of about 25 hits per 100 elderly patients in the present study.

Proving a clinical relevant reduction from 25 to 17 hits or less per 100 patients (32% relative reduction), assuming that the prevalence of inappropriate prescriptions in the control group remains constant, will imply a need for 74 peer groups in total (power of 80%; statistical significance level of 5%). This estimation takes into account the need to adjust for intra-cluster correlation, since data within the peer CME groups cannot be assumed to be independent. Furthermore, we assume the average number of GPs per peer CME group to be 7 (allowing for some withdrawals) and that the average number of patients ≥ 70 years per participating GP during the study period will be 165. Based on previous studies [46,58], the intracluster correlation coefficient is assumed to be 0.085, resulting in a variance inflation factor of 99 [59].

We will carry out post-test comparisons between the intervention and control group using cluster-adjusted chi-square and *t*-tests. Analysis of covariance may be used to adjust for imbalance of baseline levels between the intervention- and control-groups [60]. The data set will primarily be analyzed according to the cluster randomization, however, analyzes at physician- and sub-groups of physicians as well as compared to NorPD-data for GPs not participating in the study, will also be performed.

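### Peer groups are randomised within geographical strata, but none of the named comparisons includes the strata; the test stays valid but is conservative and gives up some power

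*Protocol article*

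**What the plan says.** **Allocation** (Recruitment and randomization): "Block-randomization of peer groups will be done within geographical strata, each comprised of one or more counties". Block size varies with the number of groups recruited in each stratum. The number of strata is not given.

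**Analysis** (Sample size and statistics): the plan is "post-test comparisons between the intervention and control group using cluster-adjusted chi-square" and *t*-tests. Analysis of covariance is mentioned as a possibility, and only for imbalance in baseline levels. The strata appear in none of these analyses.

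**Clustering** (same section): the article recognises that "data within the peer CME groups cannot be assumed to be independent". It inflates the sample size for this, with an intracluster correlation of 0.085 and a variance inflation factor of 99. On the level of analysis it says: "The data set will primarily be analyzed according to the cluster randomization, however, analyzes at physician- and sub-groups of physicians", together with comparisons against prescription-database data for non-participating GPs.

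**The concern.** Blocking within strata balances the arms inside each region. Regional differences in prescribing then largely cancel out of the difference between arms, so the real sampling error of that difference is smaller than under simple randomisation of groups. A two-sample test that ignores the strata estimates its error from all variation between groups, regional variation included. Its standard error is therefore too large for the design that was used.

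The consequence is a test that rejects less often than its nominal 5% under the null and has less power than the same data could give. The number of independent units is modest (74 groups required, about 80 to be recruited), so even a few points of power matter. The direction is towards missing a real effect, not towards claiming a false one.

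**Working it through.** **1. Reproduce the plan's own figures.** Inputs from Sample size and statistics: 25 versus 17 hits per 100 patients, treated as proportions 0.25 and 0.17; 7 GPs per group; 165 patients per GP; ICC 0.085; power 80%; significance level 5%, taken as two-sided.

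- Cluster size: 7 × 165 = 1155.
- Variance inflation: 1 + (1155 − 1) × 0.085 = 99.09, which agrees with the stated 99.
- Patients per arm without clustering, two proportions, continuity-corrected: 431 (406 without the correction).
- Groups in total: 2 × 431 × 99 / 1155 = 73.9, so 74, as stated.

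The sample size is built on the peer group as the cluster. It makes no use of the strata.

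**2. Effect of omitting the strata, closed form.** Let *f* be the share of the between-group variance of group means that lies between strata. The article does not give *f*; 0 to 30% is an assumed range. Take the planned case in which an unstratified design has 80% power, so that effect / SE = 1.96 + 0.84 = 2.80. Under stratified randomisation the true SE is √(1 − *f*) times the unstratified one. Then:

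- SE overstatement = 1/√(1 − *f*)
- Type I error without strata = 2 × [1 − Φ(1.96/√(1 − *f*))]
- Power without strata = Φ((2.80 − 1.96)/√(1 − *f*))
- Power with strata = Φ(2.80/√(1 − *f*) − 1.96)

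| *f* | SE too large by | Type I, no strata | Power, no strata | Power, strata | Loss (points) |
|---|---|---|---|---|---|
| 0 | 0% | 5.0% | 80.0% | 80.0% | 0 |
| 10% | 5% | 3.9% | 81.3% | 84.0% | 2.7 |
| 20% | 12% | 2.8% | 82.7% | 87.9% | 5.3 |
| 30% | 20% | 1.9% | 84.3% | 91.8% | 7.5 |

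The power of the unstratified test also rises with *f*, because the design reduces the true error whether or not the analysis uses it. The loss has to be measured against that rising figure and not against a fixed 80%.

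**3. Simulation check.** Group means were generated with 4, 6 or 9 equal strata (an assumption), allocation balanced within strata, and 20,000 runs per setting. Group-level t-tests with and without stratum terms were compared. The simulation used 72 groups so that strata were equal in size, with the effect set to give 80% power at 74 groups by the normal approximation. That is why power at *f* = 0 is about 77%.

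| *f* | Type I, no strata | Type I, strata | Power, no strata | Power, strata | Loss (points) |
|---|---|---|---|---|---|
| 0 | 4.9-5.1% | 4.9-5.1% | 77-78% | 77% | 0 |
| 10% | 4.1-4.3% | 5.0-5.3% | 79-80% | 82% | 2-3 |
| 20% | 3.3-3.5% | 5.0-5.3% | 81-82% | 86% | 4-5 |
| 30% | 2.2-2.8% | 4.9-5.0% | 83-84% | 90-91% | 7-8 |

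With few strata, the simulated type I error is a little closer to 5% than the closed form suggests. The power losses agree.

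**4. Cost in degrees of freedom.** With 74 groups the unstratified t-test has 74 − 2 = 72 degrees of freedom. With 4 to 9 strata the stratified test has 74 − 4 − 1 = 69 down to 74 − 9 − 1 = 64. The two-sided 5% critical value moves from 1.993 to between 1.995 and 1.998, which is negligible.

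**The case against.** **The analysis is valid as it stands.** This is correct. A reader might infer from the missing strata that the planned tests do not follow the randomisation at all. The article does not support that: the tests are cluster-adjusted, the data are to be analysed primarily by the randomised clusters, and the sample size inflates for the peer group. Leaving out the strata does not raise type I error.

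**The physician-level analyses.** The word "however" in the sentence on level of analysis might tempt a reader to conclude that those analyses drop the peer group, with seriously inflated type I error. If they did, the error would be inflated, by an amount that depends on a correlation between GPs in the same group that the article does not give. But the article nowhere says they ignore the group. They are additional to the primary analysis, and the same section acknowledges dependence within groups. This is a detail left unstated, not an error.

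**The size is assumed.** Neither the number of strata nor the variance they explain is given. At a share of zero there is no loss. The optional baseline adjustment could also absorb lasting regional differences and shrink the gain. Both points stand, and they are why the loss is given as a range that starts at zero.

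**An article may leave model terms to the analysis plan.** This has some force and keeps the point modest. But the article does name its tests, its one optional adjustment and its level of analysis, and what it names leaves out a design factor that it states itself.

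**Conclusion.** The point holds as a matter of efficiency. Geographical strata are used in the allocation and appear in none of the named comparisons. The resulting test is valid but conservative. For strata explaining an assumed 0, 10, 20 or 30% of between-group variance, type I error is about 5, 4, 3 or 2-3%, and about 0, 2-3, 4-5 or 6-8 points of power are lost. These figures rest on assumed variance shares, on 4 to 9 equal strata in the simulation, and on no baseline adjustment; with such adjustment the loss may be smaller. The stated 74 groups and inflation factor of 99 both reproduce and need no change. The article gives no ground for calling the primary test invalid or for attributing inflated error to the physician-level analyses.

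**What to change.** Include the randomisation strata in the primary cluster-level analysis. This can be stratum as a fixed effect in the group-level model, a stratified cluster-level t-test, or a permutation test that reassigns groups within strata. If analysis of covariance on baseline is used, keep the stratum term in that model too. The cost is one sentence and a few degrees of freedom out of about 74 to 80 groups; recruitment, conduct and sample size are unaffected.

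As a clarification, add one sentence stating that the physician-level and subgroup analyses of trial data also account for clustering by peer group, for example with a group random effect or group-robust standard errors.

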### Pilot study

With the exception of the one-day CME-course, the intervention will be piloted in one CME group before the main trial.

### Ethics and data security

Physicians participating in the peer CME groups will be given information about the objectives of the study and the practical implications this may have on their practice. They will be told that each peer CME group will be randomized to one out of two interventions (improved prescription patterns towards elderly ≥ 70 years, or improved antibiotic prescriptions for respiratory tract infections), and that they will serve as control-group for the intervention they do not take part in. Participation and data extraction are based on written, informed consent from all physicians. The aim of this study is improved quality according to well established principles for good clinical practice and should therefore not imply risks for the patients involved, and we find it unlikely that the current intervention might worsen the quality of care. The project has been presented for The Regional Committee for Research Ethics and approval from The Norwegian Social Science Data Services (NSD) has been obtained, implicating acceptance to extract prescription data. We have assessed the risk for misusing the collected data, and found this unlikely due the fact that the data are linked to de-identified ID numbers. In order to use patient identification data in the record linkage of the NorPD and EPR databases, The Norwegian Directorate for Health and Social Affairs have approved a dispensation from the Health-Professional Secrecy regulations.

### Sample size and statistics

In a pilot study (including 13 physicians) for the present study, the mean number of positive hits on our listed QIs (Table 1) made up 25 hits per 100 elderly patients during the preceding 12 months period. In accordance with this finding, we anticipate an occurrence of inappropriate prescription of about 25 hits per 100 elderly patients in the present study.

Proving a clinical relevant reduction from 25 to 17 hits or less per 100 patients (32% relative reduction), assuming that the prevalence of inappropriate prescriptions in the control group remains constant, will imply a need for 74 peer groups in total (power of 80%; statistical significance level of 5%). This estimation takes into account the need to adjust for intra-cluster correlation, since data within the peer CME groups cannot be assumed to be independent. Furthermore, we assume the average number of GPs per peer CME group to be 7 (allowing for some withdrawals) and that the average number of patients ≥ 70 years per participating GP during the study period will be 165. Based on previous studies [46,58], the intracluster correlation coefficient is assumed to be 0.085, resulting in a variance inflation factor of 99 [59].

We will carry out post-test comparisons between the intervention and control group using cluster-adjusted chi-square and *t*-tests. Analysis of covariance may be used to adjust for imbalance of baseline levels between the intervention- and control-groups [60]. The data set will primarily be analyzed according to the cluster randomization, however, analyzes at physician- and sub-groups of physicians as well as compared to NorPD-data for GPs not participating in the study, will also be performed.

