**Methods/design:**

Approximately 80 peer continuing medical education (CME) groups (about 600 GPs) in southern Norway will be recruited to a cluster randomized trial. Participating groups will be randomized either to an intervention- or a control group. The control group will not receive any intervention towards prescription patterns in elderly, but will be the target of an educational intervention for prescription of antibiotics for respiratory tract infections. A multifaceted intervention has been tailored, where key components are educational outreach visits to the CME-groups, work-shops, audit and feedback. Prescription Peer Academic Detailers (Rx-PADs), who are trained GPs, will conduct the educational outreach visits. During these visits, a set of quality indicators (QIs), i.e. explicit recommendations for safer prescribing for elderly patients, will be presented and discussed. Software will be handed out for installation in participants' practice computers to enable extraction of pre-defined prescription data. These data will subsequently be linked to corresponding data from the Norwegian Prescription Database (NorPD). Individual feedback reports will be sent all participating GPs during and one year after the intervention. Feedback reports will include QI-scores on individual- and group levels, before and after the intervention. The main outcome of this trial is the change in proportions of inappropriate prescriptions (QIs) for elderly patients ≥ 70 years following intervention, compared to baseline levels.

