### Outcome measures

Primary outcome measures will be changes in prescription patterns after the tailored educational intervention regarding the listed QIs (Table 1). Post-intervention prescription data will be collected one year after the collection of the baseline prescription data. Prescription patterns in the intervention group will be compared with the non-intervention control group, and with corresponding data (from NorPD) based on a random sample of Norwegian GPs not included in the current trial.

In addition to investigating changes in each QI, we will summarize changes for all QIs (Table 1), in order to give a total sum score for improvement potentials. The difference in total QI sum score between the intervention group and the control group will be a main outcome measure. The QI regarding regular use of the EPR function showing patient's total regular medications will not be included in this sum score. Outcome measures are summarized in Table 2.

It would also be interesting to investigate if this intervention may influence all-over mortality patterns for elderly patients targeted during this intervention as compared to corresponding elderly patients in the control group [44]. By 2006, death data are not yet included in the NorPD, but efforts are currently undertaken to include such data in the NorPD on a regular basis. A possible mortality study has not yet been elaborated in details, but this will be considered.

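### The 74-group figure matches a yes/no proportion formula although the planning quantity is a count of QI hits, so the stated 80% power is not supported for the sum score; the size of any loss cannot be determined from the article

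*Protocol article*

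**What the plan says.** Under Sample size and statistics, the protocol article reports that in a pilot with 13 physicians "the mean number of positive hits on our listed QIs (Table 1) made up 25 hits per 100 elderly patients" over 12 months. It plans to show a "reduction from 25 to 17 hits or less per 100 patients (32% relative reduction"). The control arm is held at its starting level, "assuming that the prevalence of inappropriate prescriptions in the control group remains constant". This "will imply a need for 74 peer groups in total (power of 80%; statistical significance level of 5"%). The cluster inputs are "the average number of GPs per peer CME group to be 7 (allowing for some withdrawals") and "the average number of patients ≥ 70 years per participating GP during the study period will be 165", with an intracluster correlation (ICC) of 0.085 taken from previous studies and a variance inflation factor of 99. No standard deviation of hits is given and no formula is named.

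Under Outcome measures, "we will summarize changes for all QIs (Table 1), in order to give a total sum score for improvement potentials", and the between-arm difference in that score is a main outcome. The section on quality indicators lists 14 QIs, one of which is left out of the score. The Intervention section says they cover single drugs, drug combinations and concurrent use of three or more psychotropics. The abstract words the outcome differently: "The main outcome of this trial is the change in proportions of inappropriate prescriptions (QIs) for elderly patients".

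The analysis is to use cluster-adjusted chi-square and t-tests, with analysis of covariance (ANCOVA) as an option to correct baseline imbalance.

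**The concern.** A mean of 25 hits per 100 patients is not the same as 25% of patients having a hit. One patient can score on a single drug, on a combination and on the psychotropic indicator at once. If the count was entered as a proportion, its variance was fixed at p(1-p) by the formula rather than taken from data. What is at stake is whether 74 groups, or the roughly 80 to be recruited, give the stated power for the sum score.

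The three descriptions of the main outcome (proportions of prescriptions in the abstract, a sum score, hits per 100 patients) have different denominators or scales. A reader therefore cannot settle from the text which quantity the power statement refers to.

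**Working it through.** **Inputs from the article.** Means 0.25 and 0.17 hits per patient (difference 0.08); 80% power; 5% level, taken as two-sided; 7 × 165 = 1155 patients per group; ICC 0.085. Equal allocation is assumed.

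**1. Inflation factor.** 1 + (1155 − 1) × 0.085 = 99.09, which matches the stated 99.

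**2. Reproducing 74.** The two-proportion formula with p₁ = 0.25 and p₂ = 0.17 gives 405.7 patients per arm, or 430.4 with continuity correction.
- With correction: 430.4 × 99 / 1155 = 36.9, so 37 groups per arm and 74 in total, an exact match.
- Without correction: 405.7 × 99 / 1155 = 34.8, so 35 per arm and 70 in total.

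**3. What this implies for the variance.** The formula uses 0.25 × 0.75 = 0.1875 and 0.17 × 0.83 = 0.1411, sum 0.3286. For a whole-number count X ≥ 0 with mean μ below 1, X² ≥ X, so E[X²] ≥ μ and Var(X) ≥ μ − μ² = μ(1 − μ). Equality holds only if no patient ever has two hits. The per-patient variance used is therefore the minimum for these means.

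**4. Power with other variances.** The article gives no variance for the count, so the following are assumptions. Let V be the sum of the two arms' per-patient variances and k the groups per arm.

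*Case A: the ICC of 0.085 applies to the count.* SE² = V × 99.09 / (1155 k); power from a two-sided t-test on group means with 2k − 2 degrees of freedom.

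| Per-patient variance | V | SE, k = 37 | 0.08 / SE | Power, 74 groups | Power, 80 groups |
|---|---|---|---|---|---|
| Yes/no | 0.3286 | 0.0276 | 2.90 | 82% | 85% |
| Poisson (= mean) | 0.42 | 0.0312 | 2.56 | 72% | 75% |
| 1.25 × mean | 0.525 | 0.0349 | 2.29 | 62% | 65% |

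By the normal approximation, 80% power under Poisson variance needs 7.849 × 0.42 / 0.08² = 515 patients per arm before inflation. Then 515 × 99.09 / 1155 = 44.2 groups per arm, or about 90 in total.

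*Case B: the absolute between-group variance stays at its yes/no value and only the within-group variance grows.* The between-group part is 0.085 × 0.3286 = 0.02793. SE² = [0.02793 + (V − 0.02793) / 1155] / k. Under Poisson variance the bracket is 0.02827, against 0.02819 for yes/no data. Power with 74 groups stays at about 81–82%, even with variance twice the mean.

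**5. Baseline adjustment.** With a baseline correlation of 0.5 at group level (an assumption), ANCOVA multiplies the variance by 1 − 0.25 = 0.75. In case A with 74 groups, power becomes about 83% under Poisson variance and about 74% at 1.25 times the mean.

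**The case against.** The strongest reply is that patient-level variance hardly matters here. With 1155 patients per group and an ICC of 0.085, about 99% of the variance of a group mean lies between groups (0.085 of 0.0858, in units of the patient variance). Two hits in one patient add within-group variance, which is case B, where nothing is lost. Case A also raises the between-group variance by 28% (0.42 / 0.3286) or 60% (0.525 / 0.3286). The planned figures already imply a between-group SD of √(0.085 × 0.1875) = 0.126, that is 12.6 hits per 100 around a mean of 25; case A needs 14.6 or 16.3. This reply stands as far as size goes. A reader might infer that 74 groups certainly miss 80% power, and the article does not support that. Nor does it show that case B holds: the ICC is carried over from other studies, and the spread of the count is not reported.

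A reader might also infer that chi-square is planned for the sum score. The article does not say so. It lists chi-square and t-tests together without assigning them, and the natural reading is chi-square for single yes/no QIs and the t-test for the score.

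Finally, the formula is inferred. The exact match needs the continuity correction, since 70 results without it. The exact match, the missing standard deviation and the use of the word prevalence make the inference reasonable. The stated arithmetic itself is sound; the fault lies in the outcome model.

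**Conclusion.** The point holds in a limited form. The trial is planned on a count but, by inference, sized as a proportion, with the minimum per-patient variance for that count. The stated 80% power is therefore unsupported for the sum score, which is not the same as shown to be wrong. With 74 groups the scenarios run from about 82% (between-group variance unchanged) through 72% to 62% (ICC of 0.085 carried over, with variance equal to the mean or 1.25 times the mean). These are illustrations rather than bounds, because the article does not report the spread of hits. Recruiting about 80 groups does not restore 80% power in either of the two less favourable scenarios. The differing outcome definitions are a separate, smaller fault that adds to the ambiguity.

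**What to change.** 1. Restate the power for 74–80 groups from the spread of hits in the 13-physician pilot, with the uncertainty of so small a sample. Otherwise give the 62–82% range for 74 groups and state the ICC assumption behind each end.
2. Define the main outcome in the same way in the abstract, Outcome measures and Sample size sections: total QI hits per 100 patients aged 70 or over.
3. State that the sum score is analysed on CME-group means by ANCOVA on the baseline value, as a commitment rather than an option, and that cluster-adjusted chi-square is for single yes/no QIs. Do not present ANCOVA as a guaranteed remedy: at an assumed baseline correlation of 0.5 it brings the Poisson scenario above 80% but not the 1.25 scenario.

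The cost is a less favourable or less certain power statement and some aligned wording. No extra groups are needed.

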### Participants

In Norway, specialists in general practice have to renew their clinical specialty every five years. In this renewal process, participation in a number of peer CME group meetings is compulsory, in order to stimulate continuously medical education and reflection. All GPs participating in such peer groups, on average consisting of six to eight peers, located in southern Norway, will be invited to participate in this trial. GPs using one of the four major EPRs (Infodoc^®^, WinMed^®^, ProfDoc Vision^® ^or System X^®^) are eligible for the trial. More than nine out of ten Norwegian GPs use one of these systems routinely during consultations with patients [46].

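### The variance inflation factor of 99 makes no allowance for unequal CME-group sizes; equal group weights would protect the planned power, whereas a patient-pooled test would lose some of it

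*Protocol article*

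**What the plan says.** All the sizing figures are in the Protocol article, Sample size and statistics. A fall from 25 to 17 hits per 100 patients is to be detected with "power of 80%; statistical significance level of 5" per cent, and this "will imply a need for 74 peer groups in total". The cluster size comes from two averages. For GPs the text reads "we assume the average number of GPs per peer CME group to be 7 (allowing for some withdrawals"), and the mean number of patients aged 70 or over per GP is put at 165. The assumed ICC is 0.085, "resulting in a variance inflation factor of 99".

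The same section says arms will be compared after the intervention "using cluster-adjusted chi-square and" t-tests. Covariance adjustment for baseline is optional, and the primary analysis is to respect the cluster randomisation. No weights are stated.

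The only other information on group size is in Participants, which describes the peer groups as "on average consisting of six to eight peers". The Abstract (Methods/design) plans to recruit about 80 groups and about 600 GPs.

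**The concern.** A design effect of 1 + (m − 1) × ICC is exact when every group has the same number of patients m. Here m is a product of two averages, so actual groups will differ through the number of GPs, the lists of those GPs and withdrawals. When patients are pooled, large groups get more weight in proportion to their size. With ICC × m = 0.085 × 1155, or about 98, nearly all the variance of a group's rate lies between groups, and additional patients in a large group carry almost no information. Pooling then wastes precision.

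At stake is whether 74 groups give the stated 80% power. The answer depends on a weighting choice that the text leaves open and on a CV that it does not state.

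**Working it through.** **Inputs from the Protocol article:** rates 0.25 and 0.17 (hits per 100 patients treated as a proportion), difference d = 0.08, 80% power, 5% significance, m = 7 × 165 = 1155, ICC = 0.085, 74 groups. **Assumptions:** two-sided test and 1:1 allocation (neither is stated; together they reproduce 74), and the CV of patients per group.

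**Step 1: reproduce the plan's figures.**
- Design effect: 1 + 1154 × 0.085 = 99.09, matching 99.
- Patients per arm without clustering: [1.96 × √(2 × 0.21 × 0.79) + 0.842 × √(0.25 × 0.75 + 0.17 × 0.83)]² / 0.08² = 406 after rounding up. With the continuity correction, (406/4) × [1 + √(1 + 4/(406 × 0.08))]² gives 431.
- Groups per arm, corrected: 431 × 99.09 / 1155 = 36.98, so 37 per arm and 74 in total, as stated. The uncorrected formula gives 70; one-sided versions give 56 or 60.

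Of the formulas tried, only the corrected two-sided one yields 74. On that basis power is 80.1% with equal groups, so there is almost no slack. The same 74 groups give 82.3% without the correction.

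**Step 2: let group sizes vary, pooling patients.** Design effect = 1 + ((1 + CV²) × m − 1) × ICC. At CV 0.3 this is 1 + (1.09 × 1155 − 1) × 0.085 = 107.9. The effective number per arm is 37 × 1155 / 107.9 = 396. Uncorrected power is Φ[(d√n − 1.96 × √0.3318) / √0.3286] with n = 396, which is 79.0%. For the corrected version n is replaced by (n − 1/d)²/n = (396 − 12.5)²/396 = 371.4, which gives 76.4%.

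**Step 3: equal weights per group.** The variance factor is ICC + (1 − ICC) × E[1/m]. With gamma-distributed sizes E[1/m] = 1/(1155 × (1 − CV²)). At CV 0.5, multiplied by 1155, this is 98.175 + 0.915/0.75 = 99.40, a rise of 0.3% over 99.09.

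| CV (assumed) | Pooled design effect | 74 groups, pooled: corrected / uncorrected | 80 groups, pooled: corrected / uncorrected | 74 groups, equal weights: normal / t-test, 72 df |
|---|---|---|---|---|
| 0 | 99.1 | 80.1% / 82.3% | 83.2% / 85.2% | 82.3% / 81.6% |
| 0.2 | 103.0 | 78.5% / 80.9% | 81.7% / 83.8% | 82.3% / 81.6% |
| 0.3 | 107.9 | 76.4% / 79.0% | 79.8% / 82.1% | 82.3% / 81.5% |
| 0.4 | 114.8 | 73.7% / 76.5% | 77.1% / 79.7% | 82.3% / 81.5% |
| 0.5 | 123.6 | 70.2% / 73.4% | 73.8% / 76.7% | 82.2% / 81.5% |

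A patient-weighted t-test on 72 df, the like-for-like comparison with the last column, gives 80.1%, 78.2%, 75.7% and 72.6% at CV 0.2 to 0.5.

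**Step 4: where power crosses 80% (pooled).** With 74 groups, at a CV of about 0.05 (corrected) or 0.25 (uncorrected). With 80 groups, at about 0.29 or 0.39.

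**Step 5: what CV is plausible.** The document gives none. If groups had 6, 7 or 8 GPs in equal shares, the CV of GP numbers would be 0.117. Adding independent GP lists with a CV of 0 to 0.5 gives √(0.117² + c²/7), or 0.12 to 0.22. Groups of 5 to 9 give 0.20 to 0.28, and groups of 3 to 11 give 0.37 to 0.41.

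**The case against.** The strongest reply is that nothing is miscalculated: 99 and 74 both follow from the stated inputs. Several parts of this reply stand.

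- A reader might infer that the trial fails to reach 80% power. The document does not support that as a fact, because it gives no CV. If six to eight peers is taken as the spread of sizes, the CV is about 0.12 to 0.22 and power with 74 groups is about 78–79.5% corrected or 80.5–82% uncorrected, essentially as planned. That phrase describes an average, though, so it does not bound individual groups.
- A reader might also infer that the plan commits itself to a patient-weighted chi-square. It does not. Patient pooling is the usual form of such a test, but no weights are stated. T-tests are named in the same sentence and could be run on group rates with equal weights, so the remedy may already lie within the plan. Weighting detail may properly sit in an analysis plan, and its absence here is no fault in itself.
- Recruitment of about 80 groups gives a margin over 74. The text does not assign that margin to unequal sizes, and it may be needed for groups that drop out.
- Withdrawals are already allowed for in the mean of 7 GPs (600/80 = 7.5 at recruitment), so they do not lower the mean further. They can still widen the spread.
- The effect is modest beside the uncertainty in the ICC: a CV of 0.3 equals an ICC of (107.9 − 1)/1154 = 0.093 in place of 0.085. Baseline adjustment, if used, could recover some power.

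None of this alters the fact that the design effect contains no term for size variation, or that the weights decide whether such variation costs power.

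**Conclusion.** The point holds conditionally, as an inexpensive improvement. If the main test pools patients and 74 groups are analysed, the loss against equal-sized groups is about 2 points or less up to a CV of about 0.2, 3 to 4 points at 0.3, 6 points at 0.4 and 9 to 10 points at 0.5. If about 80 groups are retained, 80% holds to a CV of 0.29 (corrected) or 0.39 (uncorrected). With equal group weights, power stays at about 81–82% throughout.

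This rests on the stated ICC and rates, a two-sided 1:1 comparison, an ICC that does not change with group size, gamma-distributed sizes for the equal-weight figures, and an assumed CV range. A material shortfall needs both patient weighting and a CV of roughly 0.3 to 0.4 or more; the document establishes neither.

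**What to change.** State that the main between-arm test compares CME-group rates, by a group-level t-test or regression, with equal or minimum-variance weights. The two nearly coincide here. With weights proportional to 1/(ICC + (1 − ICC)/m), a group of 2310 patients gets only 0.5% more weight than one of 1155 (0.08579/0.08540 = 1.005). Keep the patient-weighted estimate as a sensitivity analysis.

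If a patient-pooled test is to remain primary, restate the design effect as 1 + ((1 + CV²) × m − 1) × ICC with a stated CV, and give the resulting power for 74 and for about 80 groups.

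The cost is a change of wording, with no extra groups or data. The downside is that the estimate becomes an average over groups and no longer over patients. The two can differ if the effect varies with group size, which is why the sensitivity analysis should stay.
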